# Design and methods of a national, multicenter, randomized and controlled trial to assess the efficacy of a physical activity program to improve health-related quality of life and reduce fatigue in women with metastatic breast cancer: ABLE02 trial

**DOI:** 10.1186/s12885-020-07093-9

**Published:** 2020-07-03

**Keywords:** Metastatic breast cancer, Physical activity, Connected devices, E-health, Health-related quality of life, Fatigue

## Abstract

**Background:**

Patients with a metastatic breast cancer suffer from a deteriorated health-related quality of life and numerous symptoms such as pain, severe fatigue and a decrease of their physical fitness. As the feasibility of a physical activity program has been demonstrated in this population, ABLE02 aims to assess the efficacy of a 6 month-physical activity program using connected devices to improve health-related quality of life and to reduce fatigue in women with metastatic breast cancer.

**Methods:**

ABLE02 is a prospective, national, multicenter, randomized, controlled and open-label study. A total of 244 patients with a metastatic breast cancer, with at least one positive hormone receptor and a first-line chemotherapy planned, will be randomly assigned (1:1 ratio) to: (i) the intervention arm to receive physical activity recommendations, an activity tracker to wear 24 h a day during the whole intervention (6 months) with at least three weekly walking sessions and quizzes each week on physical activity and nutrition (ii) the control arm to receive physical activity recommendations only. Health-related quality of life will be assessed every 6 weeks and main assessments will be conducted at baseline, M3, M6, M12 and M18 to evaluate the clinical, physical, biological and psychological parameters and survival of participants. All questionnaires will be completed on a dedicated application.

**Discussion:**

An activity program based on a smartphone application linked to an activity tracker may help to improve quality of life and reduce fatigue of patients with a metastatic breast cancer. The growth of e-health offers the opportunity to get real-time data as well as improving patient empowerment in order to change long-term behaviors.

**Trial registration:**

NCT number: NCT04354233.

## Background

Approximately up to 10% of breast cancer are metastatic at diagnosis and about 20 to 30% of patients with localized breast cancer will recur with metastases [1–4]. Metastatic breast cancer (MBC) is the second leading cause of cancer-related mortality among women in Europe [5]. In France, there is no national registry that captures the prevalence and incidence of MBC. Despite therapeutic advances which transform MBC into a complex chronic condition in western countries, progress remains to be made to improve patients’ survival [6, 7]. Also, patients suffer from many detrimental symptoms such as pain, fatigue and deteriorated quality of life. Fatigue and reduced health-related quality of life (HRQoL) are related to the site of metastasis, most often bones, lung or viscera, and cancer treatments [8, 9].

The benefits of physical activity (PA) in localized breast cancer have been widely demonstrated in the literature [10–13], unlike MBC. Patients with MBC are traditionally excluded from PA interventions due to the risk of fractures, the high fatigue of patients and a worse prognosis [14]. A recent meta-analysis in patients with advanced cancer, including three studies in MBC, showed that PA interventions were feasible, safe, with a low attrition rate [15]. PA interventions in patients with advanced cancer have significantly improved functional capacities (walking distance and strength) and sleep quality, although the results on fatigue, HRQoL, *V*O_2_ peak and body composition remain heterogeneous and need to be confirmed exclusively in MBC patients [16, 17]. To date, only five PA intervention programs have been conducted exclusively in MBC patients [14, 18–21] including three feasibility studies [14, 19, 20] and two randomized controlled trials [18, 21].

The emergence of connected devices with activity trackers and smartphone applications allows patients to practice a PA at their convenience and appears as a relevant alternative to traditional PA interventions. Connected devices offer the possibility to propose PA interventions to a larger number of patients and to overcome social and territorial inequalities. These devices propose an innovative way to remotely monitor patients according to their abilities and autonomy to promote widespread PA [14, 22, 23]. Patients with breast cancer are interested in connected devices and find that activity trackers are good ways to motivate themselves and be active, but stress the importance of having personalized feedback [24–28]. Activity trackers have shown their interest in objectively measuring the number of steps, the performed activities, the quality of sleep and would also depend on the individual differences in perceptions regarding activity trackers [29–31]. Studies have shown that activity trackers would increase the PA level of patients with a chronic disease including cancer [25, 32] and that walking programs monitored by activity trackers could also improve the healthy adult participants’ quality of sleep [33].

One of the objectives of PA interventions is to limit the decline in muscle mass, also called sarcopenia, which is a major prognostic factor for cancer patients [34]. Sarcopenia may be related to advanced age but also to tumor and associates metabolic disturbances (such as insulin resistance, inflammation, oxidative stress), cancer treatment, PA decrease and nutritional deficiency [34]. Several mechanisms can influence muscle mass, and an imbalance between the synthesis (anabolism) and degradation (catabolism) [35] of muscle proteins can induce muscle atrophy [36–38]. Oxidative stress and inflammation have also been shown to be early biomarkers of sarcopenia [39, 40]. Moreover, sarcopenia has been associated with an increase of chemotherapy toxicities, a reduced HRQoL and a reduction of overall survival in MBC patients receiving capecitabine treatment [41].

The ABLE pilot study showed the feasibility to use connected activity trackers to perform a 6 month-unsupervised PA program in 51 MBC patients. The results showed patients’ motivation towards this program (94% acceptance rate), an improvement in physical performance as well as maintenance of PA levels, HRQoL and fatigue despite disease progression [20, 42]. These promising results need to be confirmed in a large multicenter, randomized controlled study. The randomized controlled trial (ratio 1:1) ABLE02 will be the first European and the most important interventional study to assess the efficacy of a PA program to improve HRQoL and to reduce fatigue in MBC women. Secondary aims will be to investigate the impact of a 6-month PA intervention on 1) overall survival and progression-free survival, 2) secondary functional and symptomatic dimensions of HRQoL, 3) fatigue, 4) physical fitness, 5) anthropometric measurements, 6) PA and sedentary level, 7) sleep disorders, 8) sarcopenia, 9) dietary patterns, 10) chemotherapy toxicities, 11) inflammation, oxidative stress and immune status 12) personality traits, 13) process of change regarding PA and 14) cancer-related cognitive impairment. For the intervention arm, patient’s acceptability for the study connected device and patient’s compliance regarding the study intervention will be evaluated.

## Methods

The study protocol was approved by the French ethics committee CPP SUD MEDITERRANEE V (ID RCB: 2019-A03277–50) and the study database was reported to the National Commission for Data Protection and Liberties (CNIL) (reference number: 2016177 v0). The study is registered on http://www.clinicaltrials.gov (NCT number: NCT04354233).

### Study design

The ABLE02 study is a prospective, national, multicenter, randomized, controlled, open-label study promoted by the Léon Bérard Comprehensive Cancer Center (Lyon, France) (Fig. 1).

**Fig. 1 Fig1:**
[figure not shown]
Participant flow chart for the ABLE02 study, France *(original flow chart)* (PA: Physical activity)

### Study population

Participants will have to meet all of the following eligibility criteria: 1) female, 2) ≥ 18 years old, 3) histologically confirmed MBC, with at least one positive hormone receptor (HR+) and HER2-, 4) first-line chemotherapy planned (or until 1 month after the chemotherapy has started) with intravenous (Paclitaxel or Doxorubicin) or per os (Capecitabine or Vinorelbine) administration, 5) Eastern Cooperative Oncology Group Performance status ≤2, 6) life expectancy ≥3 months, 7) willing to be involved throughout the study, 8) ability to practice an adapted physical activity certified by a medical certificate issued by the referring oncologist or the clinical investigator, 9) using a compatible smartphone or Tablet PC to download the application ABLE02 and Withings Health Mate (from iOS 10 and android 5.0 and more recent), 10) Internet access, 11) valid health insurance affiliation, 12) able to read, write and understand French.

Patients will not be eligible in case of 1) presence of unstable bone metastases or unconsolidated pathological fractures, 2) presence of central nervous system involvement with neurological deficits that restricts walking, 3) presence of history or co-existence of other primary cancer (except in situ cancer regardless of the site and/or basal cell skin cancer and/or non-mammary cancer in complete remission for more than 5 years), 4) severe undernutrition defined according to the Haute Autorité de Santé [43] (i.e. for women ≤70 years old: a weight loss of ≥15% in 6 months or ≥ 10% in 1 month and for women over 70 years old: a weight loss of ≥15% in 6 months or ≥ 10% in 1 month, and body mass index < 18 kg/m^2^), 5) presenting a PA contraindication (e.g., uncontrolled hypertension, uncontrolled heart disease), 6) concurrent participation in another PA study, 7) unable to be followed for medical, social, family, geographical or psychological reasons throughout the study, 8) deprived of liberty by judicial or administrative decision, 9) pregnant.

All participants will have to sign and date an informed consent form.

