#### Undernutrition and dietary patterns

Undernutrition will be assessed using the recommendations of the Haute Autorité de Santé [43]. BMI as well as percentage weight loss will be calculated (based on current weight and weight 6 months ago) and plasma albumin level determined. Caloric intakes will be evaluated with is a digital analogue scale from 0 to 10 to see how much participants are eating between “I have all eating” to “I have not eating anything”.

Dietary patterns will be assessed using a qualitative food frequency questionnaire composed of 35 items. Participants will answer the question “how frequently do you consume this product” on a Likert-type scale ranging from “never or almost” to “once per day or more” (stating quantity only for the range “once per day or more”). The questionnaire will characterize the consumption of fruits, vegetables, cereals, milk, dairy products, bread, meat, fish, poultry, eggs, starches, plant fat, desserts, sweetened products, non-alcoholic beverages, cold cuts, fried food, fast foods, preprepared meals, crackers, and snacking.

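### As printed, the severe-undernutrition exclusion adds a BMI condition for women over 70 and so, on its plain reading, is laxer for them than for younger women with the same weight loss

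*Protocol article*

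**What the plan says.** The Study population section of the Protocol article excludes patients with "severe undernutrition defined according to the Haute Autorité de Santé" and spells the definition out in a parenthesis introduced by *i.e.*, in two age groups:

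- Younger group: "for women ≤70 years old: a weight loss of ≥15% in 6 months or ≥ 10% in 1 month". No BMI condition is attached.
- Older group: "for women over 70 years old: a weight loss of ≥15% in 6 months", or at least 10% "in 1 month, and body mass index" below 18 kg/m².

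The two weight-loss limits are identical. The only difference between the groups is the BMI clause, which is joined by a comma and *and*.

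The section on undernutrition and dietary patterns returns to the same source: "Undernutrition will be assessed using the recommendations of the Haute Autorité de Santé". It names BMI, percentage weight loss and plasma albumin as the measures but prints no thresholds.

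**The concern.** Within each age group the sentence joins alternative triggers with *or*. For the BMI clause alone it switches to *and*. After a pair of alternatives, that most naturally adds a condition that must also be met. The effect is to narrow the exclusion for older women. Part of the weight loss that counts as severe undernutrition at 70 stops counting at 71, and no reason is given.

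Criterion 4 is the only one that screens for undernutrition by a stated number. Investigators in several centers apply it (Recruitment section), so a rule that can be read two ways can be applied two ways. The women it misses could be randomized to a program of at least three walking sessions a week with individual daily step goals. The Background section itself links sarcopenia to advanced age and nutritional deficiency, and to more chemotherapy toxicity, poorer quality of life and shorter survival.

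**Working it through.** The article gives no figure to reproduce here. The check is to write the rule out logically and see what each reading does. All inputs come from exclusion criterion 4.

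Let A = loss of at least 15% over six months, B = loss of at least 10% over one month, C = BMI below 18 kg/m².

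**Rules**

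- Age 70 or under: A or B.
- Over 70, plain reading: (A or B) and C.
- Over 70, narrower conjunctive reading: A or (B and C).
- Over 70, list reading: A or B or C.

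**Truth table (1 = excluded)**

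| A | B | C | ≤70 | >70: (A or B) and C | >70: A or (B and C) | >70: A or B or C |
|---|---|---|---|---|---|---|
| 0 | 0 | 0 | 0 | 0 | 0 | 0 |
| 0 | 0 | 1 | 0 | 0 | 0 | 1 |
| 0 | 1 | 0 | 1 | 0 | 0 | 1 |
| 0 | 1 | 1 | 1 | 1 | 1 | 1 |
| 1 | 0 | 0 | 1 | 0 | 1 | 1 |
| 1 | 0 | 1 | 1 | 1 | 1 | 1 |
| 1 | 1 | 0 | 1 | 0 | 1 | 1 |
| 1 | 1 | 1 | 1 | 1 | 1 | 1 |

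The younger rule excludes 6 of the 8 combinations and the older rule on the plain reading excludes 3. The three that differ are exactly those with qualifying weight loss and a BMI of 18 or more. The narrower conjunctive reading is also laxer for older women, in the one combination where only the one-month loss is met and BMI is 18 or more. Only the list reading is stricter for them. These are counts of logical cases, not proportions of patients.

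**What the plain reading requires.** At constant height, BMI falls in proportion to weight. The earlier BMI from which a loss just reaches 18 is 18 / (1 − loss):

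- 15% loss: 18 / 0.85 = 21.2.
- 10% loss: 18 / 0.90 = 20.0.

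An older woman who loses exactly 15% is therefore excluded only if she started below 21.2, and one who loses exactly 10% in a month only if she started below 20.0.

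**Two cases at age 71**

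- BMI 25, loss of 16% in six months: 25 × 0.84 = 21.0, which is not below 18. The plain reading does not exclude her and the list reading does. At age 70 she is excluded.
- BMI 17.5, no weight loss: the plain reading does not exclude her and the list reading does.

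The plain and list readings give opposite answers in both cases.

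**The case against.** The strongest reply is that *and* here only lists one more criterion. The same parenthesis uses *and* to link the two age groups, where it imposes no joint condition. A comma sets the BMI clause apart from the weight-loss pair. The undernutrition section treats BMI and weight loss as parallel indicators. An added BMI limit for older women would also give the age split an obvious purpose. On that view the defect is a loose connector, the governing rule is the cited definition, and centers screen from the full protocol, not from this article.

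Much of this stands. The list reading is possible and may be what was meant; the fix below adopts it, subject to checking the source. But it does not rescue the printed sentence. Both conjunctive readings are laxer for older women, no other text in the article decides between the readings, and the *i.e.* presents the parenthesis as the content of the definition. Whether it departs from the cited definition cannot be checked from the article.

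It is also true that the consequence is limited. The affected group is narrow: over 70, recent severe weight loss, BMI still 18 or more. Such women must also have a performance status of 2 or better, a life expectancy of at least 3 months, and the "ability to practice an adapted physical activity certified by a medical certificate", with no contraindication to physical activity and no medical obstacle to follow-up. They are not enrolled automatically, but whether they are kept out rests on individual judgement and not on the stated limit.

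**Conclusion.** The point holds. As printed and on its plain reading, criterion 4 does not exclude women over 70 with severe weight loss and a BMI of 18 or more, although the same loss excludes a woman of 70. If the list reading was intended, the sentence does not say so.

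The number of women affected cannot be derived from the article and is probably small. The criterion acts before randomization and equally in both arms, so alpha, power and the between-arm comparison do not change. What is at issue is protection of older patients and consistent screening across centers. It should be corrected, but it does not threaten the trial's conclusions. Confidence is moderate, because the intended meaning depends on a source that is not at hand.

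**What to change.** Check the criterion against the cited definition. If that confirms the BMI limit as a separate trigger, reword it as: weight loss of 15% or more in 6 months, or 10% or more in 1 month, at any age; or, for women over 70, BMI < 18 kg/m². Every older woman with a loss that would exclude a younger one is then excluded, and a low BMI alone also excludes after 70. If a joint condition really is intended for women over 70, say so explicitly and give the reason.

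The cost is the rewording of one exclusion criterion. A few women over 70 may change eligibility, in either direction depending on how centers now read the rule. Sample size and analysis need no change.

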### Recruitment

Participants will be recruited in several comprehensive cancer centers, clinics or hospitals located in France. The study will be proposed to eligible participants as soon as the decision to prescribe the first-line chemotherapy for their MBC is confirmed by the oncologist. In practice, during the pre-chemotherapy consultation (or during a consultation up to 1 month after the start of the chemotherapy), the investigator will check all eligibility criteria, explain the objectives and conduct of the study to the participant and then propose her to participate. After a sufficient period for reflection, the participant will give her consent by personally dating and signing the consent form, which will also be dated and signed by the investigator (original archived by the investigator and one copy returned to the patient).

### Randomization

At the first visit of the study, participants will be randomly assigned (1:1 ratio) to by the clinical research assistant using EnnovClinical® software (i) the intervention arm to receive PA recommendations and benefit from a 6-month APA program with connected devices or (ii) the control arm to receive PA recommendations only. Randomization will be stratified by using a dynamic minimization algorithm with three factors: the presence of visceral metastases (presence vs. absence of visceral metastases), the method of administration of chemotherapy (intravenous vs. per os) and the 6-min walking distance (6MWD) (< 455 m versus ≥455 m, based on the median observed in the pilot ABLE study).

### “ABLE02” mobile application

At baseline, the ABLE02 mobile application will be downloaded in each participant’s smartphone or tablet. This application – dedicated to the study – will be used by all patients (intervention and control arms) to complete questionnaires throughout the study. Participants will also have the possibility to complete questionnaires in a secured website. For the intervention arm, the application will also be used to monitor the number of daily steps.

### Physical activity intervention

All participants will meet a PA instructor to receive international PA recommendations at baseline (i.e. 150 min of moderate PA/week) [44].

#### Intervention arm

Participants randomized in the intervention arm will receive an activity tracker Withings Steel (Withings, Issy-les-Moulineaux, France) to wear 24 h a day during the whole intervention (6 months). The tracker will be connected to the “Withings Health Mate” application. During the first visit, the PA instructor will download the “Withing Health Mate” so that the PA data will be synchronized both in the application and the “ABLE02” mobile application. The Withing Health Mate application will be regularly used by the participant to transfer via Bluetooth activity tracker data throughout the intervention. The PA instructor will give the participant instructions on how to use the activity tracker and the mobile applications. Participants will be encouraged to practice at least three walking sessions weekly of more than 10 consecutive minutes that will be automatically detected by the activity tracker Withings Steel. Concerning the number of steps per day, the first objective will be individualized and determined according to the 6MWD performed during the baseline assessment and to participants’ preferences and capacities. We used the 6MWD data from the ABLE pilot study to identify three tertiles groups and adapt the recommendations from Tudor Locke’s paper [45, 46]. Participants who achieve less than 399 m at the 6MWD will be encouraged to perform more than 2500 steps per day, between 400 and 455 m will correspond to a goal of 5000 steps per day, between 456 and 509 m will correspond to 7500 steps per day and performance above 510 m to a goal of 10,000 steps per day. This objective will be adapted during phone calls with the PA instructor and the participant planned 15 days after inclusion, at 1 month and further on a monthly basis until the end of the intervention (6 months). During these phone calls, a new objective will be decided by the PA instructor with the participant’s agreement, according to the number of steps performed the previous week and other parameters such as the course of the disease, the potential side effects of the treatments and the patient’s preferences. The target number of steps will be set within a maximum of 1000 steps above the average number of steps in the previous week. For participants who reach 10,000 steps per day, the target will be to maintain their number of daily steps. Also, the PA instructor will encourage the participant to maintain the 3 weekly walking sessions and the achievement of the target number of daily steps. The PA instructor will use a professional dashboard to monitor the daily steps, the number of walking sessions performed, any change in the activity level, to set target number of daily steps and to adapt PA recommendations. In addition, if the number of steps is not transferred in the application for more than a week, an alert will be triggered in the professional dashboard.

In order to fight against preconceived ideas and bring knowledge to the participants, weekly quizzes with answers on PA and nutrition will be proposed through the ABLE02 application.

A messaging system and a phone line will be available for participants to contact the study team at any moment.

